#### Recruitment, assent/consent, compensation and retention.

Recruitment will be multi-faceted. CBO will distribute flyers in the community and invite interested individuals to contact the IMAGE study. CBO will also contact eligible participants directly to inform them about the project and request permission for the research team to contact them. IMAGE staff will attend relevant community events to build relationships and conduct outreach. Using a screening and consent script, research staff will follow up with girls separately from guardians or male caregivers to conduct the screening, to obtain informed consent/assent with written, electronic signature via the e-consent module in REDCap, and to confirm the contact information of legal guardians and/or participating male caregivers. We will attempt to obtain girls’ assent/consent before we contact male caregivers, but participants may be screened in any order. Girls’ refusal to participate will precede consent or permission by male caregivers and legal guardians, regardless of the screening order. Dyads will complete surveys via REDCap at baseline, 6 and 12-month follow-up. Baseline survey assessments will occur before Day 1 of the intervention via REDCap. Girls and male caregivers will each receive $60 for completing the baseline assessment and an additional $65 for completing the entire workshop weekend. Participants are compensated $70 for the 6-month follow-up and $75 for the 12-month follow-up to recognize the value of retention over time. To overcome transportation barriers to STI treatment at the University of Illinois in Chicago Hospital Health Sciences System, we will provide an additional $5 in transportation compensation if needed. Participants’ transportation barriers will be assessed when scheduled for a workshop, and participant safety will be ensured. To maximize retention, we will use the strategies that were successful in our pilot (i.e., holiday cards and monthly phone calls or text messages) [31]. We will collect contact information for girls and male caregivers in multiple forms to find the most effective communication for each participant.

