#### Secondary outcomes.

Girls and male caregiver dyads will complete baseline, 6-and 12-month assessments via self-report surveys through REDCap. Sexual behavior will be measured by condom use and the number of partners. As a part of Aim 1, we will explore the three constructs of the *Becoming a Sexual Black Woman* framework*,* using self-report surveys that capture constructs of phases of sexual development, protection, and stereotyped messaging and measures that reflect all three levels of influence (individual-, interpersonal-, societal- levels) as outlined in the HDRF Framework (Table 3).

**Table 3 pone.0320164.t003:** Aim 1 Measures for Black Girls and Male Caregivers.

Becoming a Sexual Black Woman Framework Constructs	Operational Measure	Person*	
		G	BMC

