**Phases of Sexual Development (Individual level)**			
Age of first intercourse	Age of first intercourse (vaginal, anal, and oral)	x	
Pubertal development	13-item scale describing perceived pubertal timing in comparison to peers, strategies to protect bodies and SRH, conditions influencing perceptions of bodies and behaviors and spaces feel most protected	x	
Condom self-efficacy	13-item measure of likelihood of condom use in diverse scenarios	x	
Sexual risk behavior	32-items, ARBA self-report of sexual behavior, assesses drug and alcohol use during sex (α = .79)	x	
HIV/STI knowledge, attitudes, and beliefs	18-item measure assessing factual information about HIV transmission, diagnosis, and prevention (α = .77)	x	x
Emotion regulation	20-item measure of emotion regulation, externally oriented thinking, and the ability to identify and describe feelings (α = 0.70)	x	
Coping with adverse life events	28-items self-report measures effective and ineffective ways to cope with stressful life events (α = .70)		x
Resilience	6-item, Brief resilience scale (α = .71)	x	x
Colorism	7 items, Skin Color Satisfaction Scale (α = .71)		

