**on STI incidence and risky sexual behavior:** We will evaluate treatment effects separately at 6- months and 12 months. We will also combine data to evaluate an average effect across both time points and to analyze the change from 6- to 12 months. We will analyze binary outcomes using logistic and continuous outcomes using linear regression. At a single time point, we will test the effect of the binary indicator for IMAGE vs. FUEL on the outcome, adjusting for confounders and the outcome at baseline as additional independent variables. We will use mixed-effects regression models to analyze the outcome by combining both time points, and we will include a random intercept term to account for intra-subject correlation. We will test an average effect across time points and effects on patterns of change from 6- to 12 months by including an interaction term between treatment and time. We will use survival analysis to examine sexual initiation over the course of the study. We hypothesize that non-sexually experienced girls in IMAGE will, on average, initiate sex later than FUEL participants. We will estimate the Kaplan-Meier survival curves and conduct long-rank tests to compare the two survival curves. We will use Cox regression models and its extensions (e.g., Cox’s Proportional Hazard Model with Time-Dependent Covariates) to test for the effects of other covariates such as age or socioeconomic status.

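### First sex is observed only between surveys at baseline, 6 and 12 months, but the only methods named for it take event times as known

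*Protocol article*

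**What the plan says.** The plan is in the Aim 1 analysis of the protocol article, in the paragraph comparing IMAGE and FUEL on STI incidence and risky sexual behavior. It opens with "We will use survival analysis to examine sexual initiation over the course of the study" and states a directional hypothesis about timing: "We hypothesize that non-sexually experienced girls in IMAGE will, on average, initiate sex later than FUEL participants". The methods follow: "We will estimate the Kaplan-Meier survival curves and conduct long-rank tests to compare the two survival curves", then "We will use Cox regression models and its extensions", the latter to test covariates such as age or socioeconomic status. No interval-censored or discrete-time method is named, and the event time is not defined.

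The observation times are given twice. The recruitment and retention section says "Dyads will complete surveys via REDCap at baseline, 6 and 12-month follow-up". The secondary outcomes section says "Girls and male caregiver dyads will complete baseline, 6-and 12-month assessments via self-report surveys through REDCap".

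Two girl-reported measures in Table 3 bear on initiation. One is "Age of first intercourse (vaginal, anal, and oral", with no unit or form of answer stated. The other is a general sexual-behavior survey: "32-items, ARBA self-report of sexual behavior, assesses drug and alcohol use during sex". Neither is described as giving a calendar date of first sex. The SPIRIT schedule (Fig 1) is not reproduced in the text available.

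**The concern.** The hypothesis is about when girls start, but the surveys show only the interval in which they started. A girl who answers no at baseline and yes at month 6 started somewhere in those six months. A girl who answers no at baseline, misses month 6 and answers yes at month 12 started somewhere in twelve.

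Kaplan-Meier, log-rank and Cox in their usual form need one time per event, and the natural choice is the survey at which the event is reported. That choice is harmless when every girl attends every survey. It is not harmless when surveys are missed, because a missed month-6 survey moves early events to month 12. The curve then reads too low at 6 months. If one arm attends month 6 less often, that arm appears to start later with no effect of the intervention. Starting later is what the trial hypothesizes for IMAGE, so the artefact could mimic the hypothesized result or hide it, depending on which arm attends less.

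**Working it through.** **No figure to reproduce.** The article gives no event count, hazard ratio or power for sexual initiation. What follows sizes the distortion under stated assumptions.

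**Inputs**
- Surveys at baseline, 6 and 12 months (protocol article).
- 12-month attendance b = 80%, the retention used in the article's power paragraph. b = 100% is shown for comparison.
- Month-6 attendance a: assumed 80% in both arms, or 90% in one and 70% in the other. The article expects 70%-85% retention in both arms.
- Initiation by 12 months F12 = 30%, constant hazard, no treatment effect (assumptions).
- For simulation, 141 girls at risk: 300 × (1 − 0.53), using the 53% ever-had-sex figure in the study setting section. That is an area figure, not one for trial entrants.

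**Step 1. True value at 6 months.** F6 = 1 − √(1 − 0.30) = 16.3%.

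**Step 2. What visit-dating records.** Girls who attend month 6 (share a) have events up to month 6 dated correctly. Girls who miss month 6 but attend month 12 (share (1 − a)b) are counted as event-free at 6 months whatever happened. Girls who miss both contribute nothing. With attendance unrelated to initiation:

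Kaplan-Meier estimate at 6 months = F6 × a / [a + (1 − a)b]

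| Month-6 attendance | b = 100% | b = 80% |
|---|---|---|
| 100% | 16.3% | 16.3% |
| 90% | 14.7% | 15.0% |
| 80% | 13.1% | 13.6% |
| 70% | 11.4% | 12.2% |

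For example, at a = 0.70 and b = 0.80: 16.3 × 0.70 / (0.70 + 0.24) = 12.2%. Simulations agree: about 13.4% in both arms with 20% missed, and 15.1% against 12.1% with 10% and 30% missed.

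The relative shortfall does not depend on the assumed F12. At b = 80% it is 1 − 0.85/0.97 = 12% for a = 85%, and 1 − 0.70/0.94 = 26% for a = 70%.

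**Step 3. Apparent delay.** With b = 80%, the events recorded per 100 girls are:
- a = 90%: 0.9 × 16.3 = 14.7 at month 6 and 0.8 × (30 − 14.7) = 12.2 at month 12. Mean recorded time is (6 × 14.7 + 12 × 12.2) / 26.9 = 8.7 months.
- a = 70%: 11.4 at month 6 and 0.8 × (30 − 11.4) = 14.9 at month 12. Mean recorded time is (6 × 11.4 + 12 × 14.9) / 26.3 = 9.4 months.

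The arm that attends less appears to start about 0.7 months later with no effect present.

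**Step 4. The 12-month value.** Visit-dated survival at 12 months is [1 − KM6] × (1 − F12) / (1 − a·F6), where KM6 is the Step 2 estimate. With b = 80% this gives cumulative initiation of 30.2% (a = 90%) and 30.6% (a = 70%), against a true 30%. The events are shifted in time rather than lost.

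**Step 5. The log-rank test.** With the same visit schedule in both arms, 20% dropout and 2,500 runs per setting, exact and visit-grouped times compare as follows.

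| FUEL 12-month initiation | Type I error, exact / grouped | Power at hazard ratio 0.5, exact / grouped |
|---|---|---|
| 15% | 5.2% / 5.2% | 23.3% / 23.3% |
| 25% | 4.6% / 4.6% | 37.5% / 37.6% |
| 35% | 5.6% / 5.3% | 48.6% / 48.2% |

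With 10% and 30% missed at month 6 and no effect, repeated simulations put the type I error between about 4% and 5.5%. This fits Step 4: the early deficit in one arm is made up at month 12.

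**Step 6. The alternative on the same data.** An interval-censored estimate, which treats a yes at month 12 after a missed month 6 as lying anywhere in 0-12 months, gave about 16% at 6 months in every arm and attendance setting tried.

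**The case against.** The strongest reply is that grouping hardly matters for the comparison. Step 5 bears this out: the size stays near 5%, and less than one point of power is lost when the arms share the schedule. That stands, and the point should not be presented as a threat to false-positive control.

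Second, nothing in the article predicts unequal attendance. Retention is expected to be the same in both arms, the control is time-matched, and the follow-up payments are not distinguished by arm. This also stands, so the between-arm distortion is conditional. The downward shift of the 6-month estimate needs only missed visits, which the article expects.

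Third, the Cox extensions might be read as covering grouped times. The example the article gives is time-dependent covariates, and tie handling by itself does not correct for a missed survey.

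Fourth, item wording and the event-time definition may be in the full protocol or the analysis plan. That is fair. If month and year are already asked, the data-collection part falls away.

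A reader might go further and infer that age at first intercourse is the only record, that an event cannot be placed within follow-up, or that a countable share of events would have no usable time. The article does not support this. A general sexual-behavior survey is also listed, and the schedule figure is not available. Any two attended surveys place an event in an interval, and any count of undatable events would rest on an assumed whole-year unit that Table 3 does not state.

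**Conclusion.** The point holds in limited form. On the printed text, first sex is interval-censored between the last no and the first yes, and the named methods take event times as known. If events are dated at the reporting survey, the 6-month estimate is too low by about 12% to 26% in relative terms for month-6 attendance of 85% down to 70%, with 80% attending month 12. Attendance of 90% against 70% produces a spurious gap of about 3 percentage points at 6 months (15.0% against 12.2%) and an apparent delay of about 0.7 months. The 12-month estimate and the log-rank test are little affected.

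The absolute figures rest on an assumed 30% initiation by 12 months, a constant hazard, and attendance unrelated to initiation. The relative shortfall needs only the attendance assumptions. Severity is low: sexual initiation is neither the primary outcome nor one of the named secondary outcomes, and no power claim is attached to it.

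**What to change.** Define the event interval for each girl inexperienced at baseline by the dates of her last survey answering no and her first answering yes. Replace visit-dated Kaplan-Meier and Cox with an interval-censored or discrete-time (complementary log-log) proportional-hazards model that lets the interval span a missed survey. Present interval-censored cumulative incidence curves by arm. The log-rank test may stay as a supporting comparison, with the grouping of times stated.

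If the instrument does not already record it, ask at 6 and 12 months for the month and year of first intercourse. This part is the more urgent, because an analysis plan cannot recover what was never asked. The article's study status section describes four workshops held and 15 dyads enrolled or awaiting contact, so most follow-up surveys were still to come at that point.

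The cost is one or two survey items and a change of analysis wording. The downsides are that recall of the month is imperfect and that the effect is estimated from interval data.

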#### Exploratory analysis.

Driven by the *Becoming a Sexual Black Woman* framework, we will use the regression-based causal mediation analysis approach [45] to test whether each of the individual, interpersonal, and structural (societal) level factors serve as a mediator of the intervention effect on the STI incidence, separately. Specifically, we will adopt the logistic regression model for the outcome and linear regression models for the mediators. We will report the controlled direct effect, natural direct and indirect effects, and proportion mediated with their 95% confidence intervals for each factor. We will adjust for sociodemographic characteristics collected at baseline as potential confounders in the outcome and mediator regression models. We will analyze sensitivity for unmeasured mediator-outcome confounding and report the mediational E-values [46]. We will also use a log-linear regression model for the outcome as a sensitivity analysis since our binary outcome may not be rare. We hypothesize that protection, represented by interpersonal factors such as dyad relationships, sexual communication, family risk, and protection (Table 3), would have the strongest mediation effects as it is most central to the *Becoming a Sexual Black Woman Framework.*

### 
Aim 2 mixed method data analysis

#### 
Quantitative analysis.

Survey data will be analyzed by our statistician using descriptive statistics (SAS, version 9.4), and an aggregated mean total score and means for each CBO will be calculated. Using a continuous and iterative process, we will identify contextual factors (events or statements) from observations (study notes and fidelity forms) and interviews to document what facilitates or acts as barriers to implementing IMAGE.

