#### Randomization, sample size, and power.

We will use a stratified block randomization allocation to assign girl-BMC dyads to the treatment arm (IMAGE n = 150 or FUEL n = 150) prior to baseline assessment. Power analyses determined that a sample of 300 girls – 150 IMAGE and 150 FUEL is needed to assess efficacy on the primary outcome (STI incidence). Effect size (Cohen’s h) is a function of two proportions defined by Cohen; h = .2 is a small effect, h = .5 is a medium effect, and h = .8 is a large effect. We calculated the power to detect the effect of IMAGE vs. FUEL in reducing STI incidence as measured by having any of three STIs at 12 months post-intervention using a 2-sided test with alpha = .05. The new STI outcome at follow-up was a binary variable (yes/no to testing positive for at least 1 of the 3 STIs), because the study was not powered to examine specific STI outcomes. Based on the IMARA retention rate of 86% for Black female caregiver-girl dyads in Chicago [15], we evaluated the power of STI incidence (yes/no) at 80% retention over 12- months. Based on our previous work, we assume the STI incidence is 25% and 11% at 12 months for girls in the FUEL arm and IMAGE arm, respectively, which is a small-to-medium effect size of h = .37. With the proposed sample size, we will achieve 80% power to detect the intervention effect. We also calculated the standard effect size (Cohen’s d) for group mean comparisons with 80% power for our secondary continuous outcomes, where d = 0 is defined as no treatment effect. We can detect a small-to-medium effect size with the proposed sample size (d = .37).

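### The exploratory mediation analysis names only sociodemographics as confounders; baseline mediator, baseline STI and baseline sexual experience should be added, and natural effects should not rest on a rare-outcome formula

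*Protocol article*

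**What the plan says.** All references are to the protocol article. Under Exploratory analysis, each individual, interpersonal and societal factor is tested separately as a mediator of the intervention effect on STI incidence. The outcome model is logistic and the mediator models are linear. Controlled direct, natural direct and natural indirect effects and the proportion mediated are reported with confidence intervals.

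On confounding: "We will adjust for sociodemographic characteristics collected at baseline as potential confounders in the outcome and mediator regression models". A sensitivity analysis for unmeasured mediator-outcome confounding, with mediational E-values, is also planned.

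On rarity: "We will also use a log-linear regression model for the outcome as a sensitivity analysis since our binary outcome may not be rare". The section Randomization, sample size, and power states "we assume the STI incidence is 25% and 11% at 12 months for girls in the FUEL arm and IMAGE arm, respectively".

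Elsewhere, the comparison of IMAGE with FUEL at a single time point adjusts for the baseline outcome. Data reduction and preliminary analyses has a general rule that baseline variables left unbalanced by randomisation enter later regressions. Surveys are completed at baseline, 6 and 12 months (Recruitment section), Table 3 lists age at first intercourse and sexual risk behaviour for girls, and urine is tested for STI on workshop day 1 (Primary outcome).

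**The concern.** Randomisation protects the arm-outcome and arm-mediator comparisons, but not the relation between mediator and outcome. A girl's follow-up score on communication or protection depends partly on her score before the workshop. Her earlier STI and sexual experience may influence both that score and her later infection risk, and the eligibility criteria admit girls whether or not they are sexually active. Sociodemographics may capture little of this. The efficacy model adjusts for the baseline outcome; the mediation paragraph, where such adjustment matters more, does not name it.

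At stake are the indirect effect and proportion mediated for each factor, and hence the stated hypothesis that the interpersonal (protection) factors mediate most strongly.

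The second issue is smaller. The usual closed-form natural effects from a logistic outcome model assume a rare outcome, and the plan's own rates are not rare.

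**Working it through.** **1. The plan's own figures.** Inputs: 25% and 11%, "using a 2-sided test with alpha = .05", "IMAGE n = 150 or FUEL n = 150", 80% retention (120 per arm analysed).
- h = 2·asin(√0.25) − 2·asin(√0.11) = 1.047 − 0.676 = 0.371, matching the stated .37.
- Power at 120 per arm is 81.0% (pooled proportions) or 82.0% (arcsine), matching the stated 80%.
- Expected events: 120 × 0.25 + 120 × 0.11 = 30 + 13.2 ≈ 43.

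**2. Is the outcome rare?** OR = (0.11/0.89)/(0.25/0.75) = 0.371 and RR = 0.11/0.25 = 0.440. The ratio ln(OR)/ln(RR) is 1.21. With a rare outcome it would be close to 1.

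**3. Confounding by baseline variables.** The article gives no mediator or confounder strengths, so these are assumptions. A is arm (1 = IMAGE), M0 the baseline mediator (standard normal), B baseline STI (logit = −1.2 − 0.3·M0), and ρ the weight of M0 in the follow-up mediator M. M also includes a shift a in the IMAGE arm and an effect s of B. The outcome has logit = t0 + t1·A + t2·M + g0·M0 + gB·B, with t0 and t1 solved to give 25% and 11%. Each scenario used 600,000 simulated girls. Both columns use the logistic closed form, with a·t2 estimated from the fitted models:

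NDE = exp(t1), NIE = exp(a·t2), PM = NDE(NIE − 1)/(NDE·NIE − 1).

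| Scenario (a = 0.5) | PM without M0, B | PM with M0, B |
|---|---|---|
| t2 = −0.6; no direct baseline paths (g0 = gB = 0); ρ = 0.5, s = 0 | 18.7% | 18.8% |
| t2 = −0.6; g0 = −0.3, gB = 0; ρ = 0.5, s = 0 | 23.2% | 17.8% |
| t2 = −0.6; g0 = −0.3, gB = 0.9; ρ = 0.5, s = −0.3 | 25.1% | 16.7% |
| t2 = −0.3; g0 = −0.3, gB = 0.9; ρ = 0.6, s = −0.3 | 17.6% | 8.6% |
| t2 = 0 (no mediation); g0 = −0.3, gB = 0.9; ρ = 0.6, s = −0.3 | 7.9% | −0.1% |

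Hand check of the last row, unadjusted: NDE 0.419 and NIE 0.881 give 0.419 × (−0.119)/(0.369 − 1) = 0.079. A separate simulation of a null mediator gave about 6%, also falling to 0% on adjustment.

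**4. The rare-outcome formula, with no confounding.** M is normal with unit variance and a shift a. Exact counterfactual risks come from numerical integration, again calibrated to 25% and 11%. The like-for-like comparison is with exact odds ratios.

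| a, t2 | PM, closed form | PM, exact ORs | PM, risk difference |
|---|---|---|---|
| 0.5, −1.0 | 30.9% | 33.1% | 37.0% |
| 0.5, −0.7 | 22.2% | 23.1% | 26.3% |
| 0.3, −0.7 | 12.4% | 13.0% | 15.0% |

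First row, closed form: NIE = exp(−0.5) = 0.607 and NDE = 0.532, so PM = 0.532 × (−0.393)/(0.323 − 1) = 0.309. From exact ORs: NDE 0.579 and NIE 0.641, so PM = 0.579 × (−0.359)/(0.371 − 1) = 0.331. The error is 2.2, 0.9 and 0.6 points. The remaining gap to the last column is a change of scale.

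**The case against.** Several points on the other side have force.

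- **The text excludes nothing.** It lists sociodemographics without saying that they are the whole set, and an article may leave a full covariate list to an analysis plan that is not shown. That is why the point concerns what is named. It still stands, because this paragraph does specify the models and the confounders and passes over the baseline variables most relevant to the mediator-outcome relation.
- **Safeguards exist.** E-values gauge how strong unmeasured confounding would have to be; they do not replace adjustment for variables already measured. The imbalance rule could bring in baseline STI, but only if the arms differ on it, which is not the criterion for mediator-outcome confounding.
- **The rarity problem is acknowledged.** A log-linear analysis is already planned, and the article does not say that closed-form formulas will be used. The log-linear model is not exact either when the true model is logistic: in the a = 0.5, t2 = −1.0 case a large-sample modified Poisson fit gave PM 32.6%, against 30.9% from the logistic formula and 37.0% on the risk-difference scale. Simply swapping the two models would therefore not settle the matter.
- **Precision is poor.** With 240 girls and about 43 events, simulated PM estimates in that case ranged (95%) from about 8% to above 140%, far wider than a 2-point error.

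A reader might infer that the mediation results are certainly biased, that the rarity error reaches 6 points, or that mediators will be ranked by baseline risk. The documents do not support these. The first needs direct baseline-to-STI paths that the article does not quantify, the second compares odds ratios with risk differences, and no calculation backs the third.

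**Conclusion.** The point holds as a minor one. The named adjustment set omits measured, plausible mediator-outcome confounders. Under the assumed strengths, leaving them out moves the proportion mediated by between 0 and about 9 points, and can give a null mediator an apparent 6-8%. If the baseline variables act on STI only through the follow-up mediator, there is no bias.

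The rare-outcome issue is real, because the plan assumes 25% and 11%, but it is worth only about 1-2 points on the odds-ratio scale in the cases worked.

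The analysis is exploratory, so the primary efficacy conclusion does not depend on it.

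**What to change.** 1. Add the baseline value of the same mediator, baseline STI and baseline sexual experience to both the mediator and the outcome models, alongside the sociodemographics.
2. Keep the planned sensitivity analysis and E-values, described as addressing what remains unmeasured.
3. Compute natural effects without the rare-outcome approximation (for example, by averaging predicted risks from the logistic model over the mediator distribution), or report the log-linear result alongside as a main result. State the scale on which the proportion mediated is reported.

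No new data are needed. The cost is wording plus a few extra model terms. With about 43 expected events these will strain the outcome model somewhat, so the sociodemographic list should be kept short.

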**Protection (Interpersonal level)**			
Caregiver-girl relationship and attachment	16-item scale, Child’s Report of Parent Behavior Inventory (CRPBI) perceived relationships of caregivers and girls	x	x
Sexual communication	20-item measure of perceived quality and quantity of risk-specific communication (e.g., having sex, condoms, and AIDS) (α=.65-.87)	x	x
Family risk and protection	38-item assessing 6 number of subscales on Family Conflict, Attitudes toward Attachment, Prosocial Involvement, Attitudes toward Drug Use (α = .66–.76)	x	x
Gendered racial socialization for BW	63- item, Gendered Racial-Ethnic Socialization Scale (GRESS) for Black women scale, gendered racial-ethnic socialization messages from caregivers regarding their identities (α = .67–.96)	x	

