**Stereotyped Messaging (Societal level)**			
Stereotyping	11-item, to assess the extent to which participants endorse the sexualized stereotypes about Black women, to reflect the hypersexual and promiscuous nature of stereotypes. (α = 0.93)	x	x
Sexual objectification	11 item, Interpersonal Sexual Objectification Scale, experiences with having bodies evaluated (α = 0.91)	x	
Justification of Violence Scale	27-item, extent to which participants condoned IPV toward women when they behave in stereotype-consistent ways, (α = .99) for female and (α = .99) male sample	x	x
Everyday discrimination	5-item, Everyday Discrimination Scale, discrimination in everyday activities (α = .77)	x	x
G = Girls and BMC = Black male caregivers			

### 
Aim 2 implementation measures

Aim 2 data will be generated from the environmental scan, direct observations (fidelity ratings), study notes from meetings, semi-structured interviews documenting CBO personnel experiences hosting IMAGE (Table 4), and surveys (Table 5) of the CBOs’ attributes. Perceptions of acceptability, feasibility, and appropriateness of IMAGE will be assessed during *Preparation* after the *Rollout* phases, as well as views regarding IMAGE ownership during the *Sustain* phase.

**Table 4 pone.0320164.t004:** Aim 2 EPIS-Informed Semi-Structured Qualitative Interview Questions.

Outer Context
• What are your support structures/who supports your CBO (i.e., inter-organizational coalitions and relationships between entities, government, and funders)?
Inner Context
• How has the implementation of IMAGE been at your CBO? *Probe*: Did IMAGE address the needs of CBO families? • Tell me about your experience hosting IMAGE at your facility. *Probes*: How easy or difficult was it to run IMAGE at your CBO? Did IMAGE impact your work for the CBO? • What did you like and dislike about the IMAGE program? *Probes*: What were some of the inconveniences, difficulties, and problems you experienced while running IMAGE? Were you provided adequate support to host IMAGE? • What barriers do you foresee in running IMAGE at your CBO? *Probe*: What ideas do you have to overcome those barriers?
Bridging Factors
• How would you describe the relationship between you and the IMAGE team at UIC? *Probes*: What would you want to change about IMAGE? Do you feel like IMAGE aligns with your CBO mission?
Innovation

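### Mediation models use uncorrected scale scores, which tilts the comparison of two protection measures with three societal scales against the plan's own hypothesis

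*Protocol article*

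**What the plan says.** The Protocol article, under Aim 1 analysis, Exploratory analysis, tests whether each individual, interpersonal and societal factor will "serve as a mediator of the intervention effect on the STI incidence, separately". The method is stated: "we will adopt the logistic regression model for the outcome and linear regression models for the mediators". Controlled direct effects, natural direct and indirect effects and the proportion mediated are to be reported, with 95% confidence intervals, for each factor.

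Two sensitivity analyses are named. One is a log-linear outcome model. The other concerns confounding: "We will analyze sensitivity for unmeasured mediator-outcome confounding and report the mediational E-values". Neither deals with error in the mediator.

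The section also states a ranking in advance. Protection, described by dyad relationships, sexual communication, and family risk and protection, "would have the strongest mediation effects as it is most central to the" framework. No test or decision rule is attached to this ranking.

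Table 3 prints the reliabilities. At the protection level, sexual communication has "e.g., having sex, condoms, and AIDS) (α=.65-.87" and family risk and protection has "Attitudes toward Drug Use (α = .66–.76". Gendered racial socialization is given as .67-.96. The caregiver-girl relationship scale, "Child’s Report of Parent Behavior Inventory (CRPBI) perceived relationships of caregivers and girls", has no alpha. At the societal level, stereotyping is .93, sexual objectification .91 and everyday discrimination .77. Justification of violence measures how far participants "condoned IPV toward women when they behave in stereotype-consistent ways, (α = .99) for female" respondents, with the same value for males. Individual-level alphas, where given, run from .70 to .79.

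**The concern.** Random error in a mediator score leaves the arm-to-mediator difference unbiased but weakens the estimated mediator-to-STI slope. The indirect effect is built from both, so it shrinks roughly in proportion to the scale's reliability. The total effect does not change, so what the indirect effect loses appears as direct effect.

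Two things follow. First, for every imperfect scale the proportion mediated is understated and the direct effect overstated, whatever the ranking. Second, when mediators of unequal reliability are compared, the order partly reflects scale quality. Two of the three constructs named in the hypothesis have modest alphas, while three of the four societal scales have very high ones. A true lead for caregiver protection, the mechanism on which the programme is built, could be narrowed or reversed for this reason alone. E-values for unmeasured confounding would not reveal it.

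**Working it through.** The plan gives no computed figure on this point, only alphas, so there is nothing of its own to reproduce.

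**Inputs.** Alphas are from Table 3 as listed above. Path sizes are assumptions, because the article gives none.

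**Step 1: shrinkage of one indirect effect.** With arm-to-mediator path a, mediator-to-outcome path b and reliability ρ, the observed indirect effect is about a × (ρb), that is, ρ times the truth. A simulation checked this for a logistic outcome (N = 1,000,000; a = 0.5; b = -0.8; direct effect -0.3; within-arm mediator SD 1; error variance (1-ρ)/ρ):

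| ρ | Share of true indirect effect kept | Proportion mediated (error-free 0.525) |
|---|---|---|
| .65 | .63 | .329 |
| .66 | .64 | .335 |
| .76 | .74 | .390 |
| .77 | .75 | .395 |
| .87 | .86 | .451 |
| .91 | .90 | .474 |
| .93 | .92 | .485 |
| .99 | .99 | .520 |

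**Step 2: the handicap in a comparison.** The true advantage a mediator needs merely to tie is the ratio of reliabilities, ρ(comparator)/ρ(protection).

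- Against the three high-alpha societal scales: .99/.65 = 1.52; .91/.65 = 1.40; .91/.76 = 1.20; .91/.87 = 1.05.
- Against everyday discrimination: .77/.65 = 1.18; .77/.87 = 0.89. The direction depends on where in its range sexual communication falls.
- Against individual-level measures: .79/.65 = 1.22; .70/.87 = 0.80. Again there is no clear direction.
- Socialization at its upper end: .91/.96 = 0.95, so no handicap.

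**Step 3: summed scores.** The protection alphas are ranges, probably across subscales; Table 3 mentions six subscales for family risk. The reliability of a sum of k subscales with common alpha α and inter-subscale correlation r (assumed) is 1 - k(1-α)/[k + k(k-1)r].

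- k = 6, α = .66, r = .2: 1 - 2.04/12 = .83.
- k = 6, α = .76, r = .5: 1 - 1.44/21 = .93.
- k = 2 over the same range of inputs: about .72 to .84.

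At six-subscale reliabilities of .83-.93, the handicap runs from .91/.93 = 0.98 to .99/.83 = 1.19.

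**Step 4: effect on the order at trial size.** Simulations used n = 240 (80% of 300), two independent mediators fitted separately, a = 0.4, b = -0.6, an assumed baseline risk and 3,000 trials per setting. Ranges are across repeated runs. With equal true mediation, the protection mediator came first in:

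- 26-28% of trials at .66 v .99
- 38% at .76 v .93
- 39-40% at .76 v .91
- 43-44% at .85 v .95
- 46-48% at .87 v .91
- 49-51% with error-free scales

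Dividing each indirect effect by its reliability brought the figure back to about 47-49%. When protection was truly 1.5 times as strong, it came first in 50-52% at .66 v .99 and 74-75% at .87 v .91, against 73-77% error-free.

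**The case against.** The strongest objection is scope. This is an exploratory analysis in a journal article, and a measurement-error correction could sit in an analysis plan that is not shown. That lowers the severity. It does not remove the point, because the article fixes the models, names its sensitivity analyses, prints the alphas and commits to a ranking.

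A reader might infer that the protection level as a whole is the most attenuated, so that the whole ranking is biased against it. Table 3 does not support that. Individual-level alphas (.70-.79) and everyday discrimination (.77) are no better than those of the protection measures. Socialization reaches .96, and the dyad relationship, the first factor the hypothesis names, has no alpha. Nor is it right that protection is measured far less reliably throughout: at .87 against .91 the difference is slight.

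It is also fair that ranges are being set against single values, and that summing could close much of the gap. The section on data reduction plans summary scores for relationship and communication, but names none for family risk.

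Finally, the order is noisy anyway. At the planned rates there would be about 120 × .25 + 120 × .11 = 43 STI cases, and even error-free scales miss a true 1.5-fold lead in roughly a quarter of simulated trials. Among the affected comparisons the tilt runs against the authors' hypothesis, so it does not manufacture a false confirmation. All of this stands, and it supports treating the point as minor.

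**Conclusion.** The concern holds in a limited form. Without correction, indirect effects and proportions mediated are understated for every imperfectly measured mediator, and direct effects are overstated. Sexual communication and family risk and protection keep about 63-86% of their true indirect effect, against about 90-99% for stereotyping, sexual objectification and justification of violence. Those particular comparisons carry a handicap of about 1.05 to 1.52, and less if subscales are summed. The risk is a false failure to find protection leading over these three scales.

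These sizes assume classical non-differential error, Table 3's alphas as the within-arm reliabilities in this sample, and no confounding by other mediators in the separate models. The ranking percentages also depend on assumed path sizes and independent mediators.

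Severity is minor. The analysis is exploratory, has no decision rule, and does not touch the primary or secondary efficacy conclusions.

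**What to change.** Add a sensitivity analysis that corrects each multi-item mediator model for measurement error. Use either a latent mediator, or a single indicator with its error variance set from the trial's own within-arm reliability of the score actually used. Report corrected and uncorrected indirect effects side by side. Do not claim that one level mediates more than another unless the order holds in both analyses or the disagreement is stated.

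The cost is a few sentences of analysis-plan wording and modest programming; no new data are needed. The downside is wider intervals and dependence on the reliability estimate.
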